#### Safety outcomes

2.5.3

General physical examinations will be recorded at each visit point, including temperature, respiration, heart rate, and blood pressure.Routine laboratory tests for blood and urine, liver and kidney function, coagulation function and electrocardiogram (ECG) will be conducted at baseline and at the end of treatment.

#### Metabolomics analysis

2.5.4

Blood samples will be collected for metabolomic analysis. Liquid chromatography-mass spectrometry (LC-MS) and gas chromatography-mass spectrometry (GC-MS) will be used to identify chemical and biological fingerprints, screen bioactive components, and explore the potential metabolic pathways and targets of SGJY in the treatment of depressive state after ACS. Participants will be required to fast for at least 8 hours prior to blood collection. A 5 mL blood sample will be collected into heparin sodium anticoagulant tubes, centrifuged, and stored in Eppendorf tubes at −80°C.

#### Adverse events

2.5.5

This study will monitor all adverse events (AEs), serious adverse events (SAEs), and adverse drug reactions (ADRs). All AEs must be promptly documented in both the source documents and the CRFs upon discovery. If an AE is classified as an SAE or a serious ADR, it must be reported in accordance with the applicable reporting procedures.

Due to the nature of the underlying diseases in this study, participants may experience clinical deterioration during the observation period, potentially requiring hospitalization or resulting in life-threatening events. However, MACCE is a predefined efficacy outcome in this study. Therefore, the occurrence of these events will not be documented as AEs. Likewise, hospitalizations or deaths resulting from these events will not be reported as SAEs.

All AEs must be followed until the participant’s condition returns to baseline (pre-treatment) levels or stabilizes. Investigators are responsible for continuous monitoring to ensure participant safety throughout the study.

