##### Secondary outcomes

2.5.2.2

The secondary outcomes are as follows:

Major Adverse Cardiovascular and Cerebrovascular Events (MACCE), defined as a composite of cardiovascular death, nonfatal myocardial infarction, revascularization, and stroke. These events will be recorded throughout the study period. The cumulative incidence of MACCE will be analyzed over the 36-week follow-up period.The Seattle Angina Questionnaire (SAQ) evaluates five health domains in patients with stable coronary artery disease: physical limitation, anginal stability, anginal frequency, treatment satisfaction, and disease perception.The Patient Health Questionnaire-9 (PHQ-9), Hamilton Anxiety Scale (HAMA), Generalized Anxiety Disorder-7 (GAD-7) and Dimensional Anhedonia Rating Scale (DARS) will be administered at baseline, and at weeks 4, 8, and 12 post-treatment, as well as at the 36-week follow-up, to assess anxiety and depressive symptoms.The Short Form-36 Health Survey (SF-36) will be administered at baseline, and at weeks 4, 8, and 12 post-treatment, as well as at the 36-week follow-up, to assess patients’ quality of life.The Montreal Cognitive Assessment (MoCA) will be administered at baseline, and at weeks 4, 8, and 12 post-treatment, as well as at the 36-week follow-up, to evaluate cognitive function.Improvement of Indicators in Cardiopulmonary Exercise Testing (CPET): (a) Metabolic Equivalents (METs), exercise time, Peak oxygen uptake (PeakVO2), oxygen pulse (VO2/HR), oxygen uptake relative to work rate (ΔVO2/ΔWR), and ventilatory anaerobic threshold (VAT). These parameters reflect exercise tolerance and cardiovascular function. (b) Breathing reserve (BR), the dead space volume/tidal volume ratio (VD/VT) and breathing frequency (Bf). These parameters reflect ventilatory function. (c) Partial Pressure of End-Tidal Carbon Dioxide (PETCO2), and the ventilatory equivalent of carbon dioxide (VE/VCO2 slope): These reflect the efficiency of pulmonary gas exchange. CPET includes over 50 indicators, each of which holds prognostic significance across cardiovascular conditions.Inflammatory cytokines (IL-1β, IL-6, GDF15, and sCD40L) and hormones related to the HPA axis—corticotropin-releasing factor (CRF), adrenocorticotropic hormone (ACTH), and cortisol—will be measured. BDNF will also be assessed. Blood samples will be collected before treatment and on the day of the end-of-treatment.

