### Statistical analysis

2.7

Statistical analyses were performed using SAS version 9.3 (SAS Institute Inc., USA) and included baseline characteristics, efficacy, and safety outcomes. A p-value of < 0.05 was considered statistically significant. The efficacy analysis will follow the intention-to-treat (ITT) principle. The Full Analysis Set (FAS) includes all randomized patients, excluding those who severely violated the inclusion criteria or did not receive any assigned treatment. Baseline characteristics will be analyzed within this set to assess comparability. The Per-Protocol Set (PPS) includes patients who completed the planned treatment regimen, whereas the Safety Set (SS) consists of patients who received at least one dose of the study treatment and underwent safety evaluation. Efficacy analysis will be primarily applied to the FSA and PPS. Safety evaluations will be performed using the SS.

For primary and secondary outcomes, continuous data will be analyzed using the t-test or Mann-Whitney U test; categorical data will be assessed using the Chi-squared test or Fisher’s exact test; and ordinal data will be evaluated using the Mann-Whitney U test. To account for potential center effects in this multicenter trial, analyses will be stratified by study site. Efficacy will be evaluated using the Cochran-Mantel-Haenszel (CMH) test to adjust for inter-center variability.

If baseline characteristics between groups are imbalanced, confounding factors that are difficult to control or unmeasured may be included as covariates in an analysis of covariance (ANCOVA) or logistic regression model. Between-group differences in efficacy will be assessed using least-squares means (LSMEANs) and their 95% confidence intervals to minimize the impact of confounding factors.

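### MACCE are barred from the AE and SAE records with no exception for suspected drug causality, and the stated MACCE analysis window, read literally, leaves out the 12 treatment weeks

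*Protocol article*

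**What the plan says.** **The exclusion.** Section 2.5.5 (Adverse events) gives its reason first: "However, MACCE is a predefined efficacy outcome in this study". It then states that "the occurrence of these events will not be documented as AEs" and, for their consequences, that "hospitalizations or deaths resulting from these events will not be reported as SAEs". Section 2.5.2.2 (Secondary outcomes) gives the composite, "defined as a composite of cardiovascular death, nonfatal myocardial infarction, revascularization, and stroke".

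**The safety evaluation.** The Abstract bases safety on safety indicators and recorded adverse events. Section 2.5.3 lists vital signs, blood and urine tests, liver and kidney function, coagulation and ECG. Section 2.7 adds: "Safety evaluations will be performed using the SS". MACCE is not named in any of these places.

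**The efficacy evaluation.** Section 2.5.2.2 says MACCE are recorded across the whole study, and Table 2 schedules them at every visit from V2 (week 4) to V7 (week 48). On analysis, the same section says: "The cumulative incidence of MACCE will be analyzed over the 36-week follow-up period". Table 2 heads V2 to V4 as the 12-week intervention period and V5 to V7 as the 36-week follow-up period.

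**The concern.** Exempting endpoint events from expedited SAE reporting is common, and on its own would not call for comment. This rule goes further in two ways. It stops the events from being documented as AEs at all, and it applies even when the investigator suspects the study drug.

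The article offers one other place where such events would be seen, the MACCE efficacy analysis. Its stated window starts when treatment ends. If both sentences are followed as written, a stroke or cardiovascular death in week 6 is collected but enters neither the safety tables nor the stated MACCE analysis.

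The trial sets out to assess efficacy and safety in patients 2 to 12 weeks after ACS. A favourable safety conclusion would rest on tables without the most serious events to be expected in that population.

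**Working it through.** The point is mainly textual. The plan states no expected MACCE count, so there is no figure of its own to reproduce.

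**Step 1: follow an on-treatment MACCE through the plan.** Take a nonfatal infarction in week 6.

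| Route | Rule | Outcome |
|---|---|---|
| AE record | 2.5.5: MACCE not documented as AEs | absent |
| SAE report of the resulting admission | 2.5.5: not reported as SAE | absent |
| Safety Set tables | Abstract, 2.5.3, 2.7: recorded AEs, laboratory tests, vital signs, ECG | event absent |
| MACCE collection | 2.5.2.2 and Table 2: V2 to V7 | recorded |
| MACCE cumulative incidence | 2.5.2.2: 36-week follow-up, weeks 12–48 in Table 2 | absent if read literally |

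For an infarction in week 20 the last row becomes present, but the event is still missing from the safety evaluation. The first three rows therefore do not depend on how the 36-week sentence is read. Only the last row does.

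**Step 2: illustrative scale.** Inputs: N = 148 (2.3.3), and from the Introduction a two-year risk of recurrent coronary events of up to 32.5% and a five-year cardiovascular mortality of 11.2%. Assumptions: constant hazard, the same risk in both arms, and coronary event risk as a proxy for the MACCE composite. The Introduction gives 32.5% as a high-end figure and for a different endpoint, so half and a quarter of it are shown as well.

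Expected patients with an event by week w = 148 × [1 − (1 − R)^(w/104)].

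- R = 0.325: week 12, 148 × 0.0443 = 6.6; week 48, 148 × 0.1659 = 24.6.
- R = 0.1625: week 12, 148 × 0.0203 = 3.0; week 48, 148 × 0.0786 = 11.6.
- R = 0.08125: week 12, 148 × 0.0097 = 1.4; week 48, 148 × 0.0384 = 5.7.

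Cardiovascular deaths = 148 × [1 − (1 − 0.112)^(w/260)], which is about 0.8 by week 12 and about 3.2 by week 48, both arms together.

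Under 2.5.5 none of these would be in the AE or SAE tables, whichever rate applies.

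**The case against.** **The events are not lost.** Section 2.5.2.2 records MACCE throughout, and Table 2 collects them at weeks 4, 8 and 12. Collecting them on treatment fits poorly with an intention to discard them, so the 36-week sentence may be loose condensation. The comparison by arm in the FAS, which excludes untreated patients, would largely overlap the Safety Set. This stands: much of the defect is about which table shows the events, and the fix is cheap because the data exist. It does not remove the stated window, nor the absence from the safety evaluation.

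**Keeping endpoint events off SAE forms is a recognised practice.** This also stands, and it is why the remedy below does not require an SAE form for every MACCE. It does not cover a bar on documentation, or the lack of an exception for suspected causality.

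**Two stronger readings are tempting and not supported.**

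- A reader might infer that the section contradicts itself, since it opens by promising to monitor all AEs, SAEs and ADRs. It does not: a general rule is followed by an explicit, reasoned exception.
- A reader might infer that the Safety Set cannot show any cardiovascular harm. That is too strong. On the natural reading, where the excluded events are MACCE only, arrhythmia, heart failure or an angina admission without revascularization remains an AE or SAE. Non-cardiovascular deaths do too. ECG and vital signs are safety measures.

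**Conclusion.** The point holds in this form: as written, the safety evaluation omits cardiovascular death, nonfatal infarction, revascularization and stroke, including any suspected to be drug-related. If the 36-week sentence is taken literally, those occurring during treatment are also missing from the stated efficacy analysis. The first part rests on the plain text of 2.5.5, 2.5.3 and 2.7. The second rests on a literal reading of one sentence and could prove to be a drafting slip.

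The size is about 1.4 to 6.6 patients with an event in weeks 0–12 and about 6 to 25 by week 48, with about 0.8 and 3 cardiovascular deaths. These figures rest on constant hazard and a proxy endpoint. The upper end should not be read as the expected count: trial patients are haemodynamically stable, and NYHA III–IV and LVEF below 35% are excluded. This is worth correcting before analysis. It does not threaten the primary HAMD-17 comparison.

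**What to change.** 1. Keep MACCE as a secondary efficacy outcome, but state in 2.5.2.2 that cumulative incidence is analysed from randomisation to week 48, in line with the recording window there and in Table 2.
2. Add to the safety evaluation a descriptive table by arm, in the Safety Set, of MACCE, each component and all-cause death, for weeks 0–12 and 0–48.
3. Reword 2.5.5 so that any exemption applies to expedited reporting only and not to documentation, does not extend to events suspected to be drug-related, and names MACCE explicitly as the events it covers.
4. Reconcile 2.5.2.2, 2.5.5 and Table 2. Because the AE row of Table 2 ends at V4, make clear that non-cardiovascular deaths after week 12 are noted at the V5 to V7 contacts, so that the all-cause death table is complete.

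The cost is a few extra tables and amended wording. MACCE are already collected at V2 to V7, so no visits are added.

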### Data management

2.6

#### Completion and management of CRF

2.6.1

Researchers must accurately and thoroughly collect original data and use it to complete the CRF. To ensure strict adherence to the research protocol, the principal investigator will designate a clinical monitor to conduct regular supervisory visits to the research sites. Both paper and electronic research data must be stored for a minimum of five years, and biological specimens will be disposed of ethically after monitoring, in accordance with participants’ rights and interests.

#### Data entry and modification

2.6.2

This study will collect participants’ electronic medical record information through an Electronic Data Capture (EDC) system. To ensure the accuracy of the data, data entry will be performed independently by two designated data entry clerks from each research unit, who will also proofread the data. For any queries in the Case Report Form, the data manager will fill out a Data Query Form (DRO) and send an inquiry to the researchers. The data manager will then modify the data based on the researchers’ responses.

#### Data locking and review

2.6.3

Upon completion of data entry, the principal investigator and statistical analysts will lock the data while remaining blinded, after which no further modifications will be allowed. A line-by-line verification will then be conducted to review the entries made by both data entry personnel. A random sample of CRFs will be selected and cross-checked against the data in the EDC system to ensure consistency with the original source data.

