#### Blinding

2.3.2

This study adopts a double-blind design. The first level blinding corresponds to the group codes linked to medication numbers (Group A, Group B), while the second level pertains to the treatments assigned to each code (SGJY group or placebo control group). Both levels of blinding will be documented by statisticians independent of trial analysis. Two sealed copies of the blinding records will be maintained separately by the principal research center. These blinding records must remain unopened throughout the study period. The first unblinding for the statistical analyst will conduct after data lock, and the second after completion of the statistical analysis. Emergency envelopes may only be opened in the event of a medical emergency (serious adverse event, rapidly deteriorating condition). Each envelope will contain designated fields for the signature, date, and reason for unblinding by the person who opens it. Cases withdrawn due to therapeutic reasons should not be unblinded. The unblinded case materials must be kept intact.

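### The database is locked against any change before the line-by-line verification and, by its place in the text, the sampled CRF check, so errors these checks find cannot be corrected as the plan is written

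*Protocol article*

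**What the plan says.** Section 2.6.3 (Data locking and review) has the principal investigator and the statistical analysts act once data entry is complete. The effect of the lock and the step that follows it stand together; they will "lock the data while remaining blinded, after which no further modifications will be allowed. A line-by-line verification will then be conducted". The purpose of that verification is to compare the two clerks' work: "A line-by-line verification will then be conducted to review the entries made by both data entry personnel". The paragraph ends with the sampled check: "A random sample of CRFs will be selected and cross-checked against the data in the EDC system to ensure consistency with the original source data".

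Section 2.3.2 (Blinding) sets the times for opening the codes: "The first unblinding for the statistical analyst will conduct after data lock, and the second after completion of the statistical analysis". The first level shows which participants are in Group A and which in Group B. The second level shows which group receives SGJY.

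Other controls are described elsewhere. Section 2.6.2 has independent entry by two clerks who also proofread, and a query route by which the data manager changes data after the researchers reply. Section 2.6.1 has regular monitoring visits, and section 2.8 has regular audits of source data at the sites.

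**The concern.** A check of entries against each other, or against the CRF, is useful for the analysis only if a discrepancy can still be corrected. The stated order removes that possibility: the rule against changes takes effect first and the checks follow. Someone following the text would either leave a known error in the analysed data or break the lock.

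Breaking the lock raises a second issue. The first unblinding depends on the lock and not on completed verification, so the analyst may already hold the A/B codes when a late correction is made.

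The primary outcome makes this more than a formality. It is a responder classification with a sharp cut at a 50% reduction in HAMD-17, so a single mis-keyed point can change a participant's status.

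**Working it through.** The plan gives no figure for data error, so there is none to reproduce. The check is mainly of the order of steps.

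**Order of steps in sections 2.6.3 and 2.3.2**

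1. Data entry is completed.
2. The data are locked under blinding, and changes are ruled out from that point.
3. Line-by-line verification of both clerks' entries. The word "then" in "A line-by-line verification will then be conducted to review the entries made by both data entry personnel" places this after step 2.
4. Sampled CRF-to-EDC comparison. The sentence has no timing word, so its place after lock is inferred from its position after step 3.
5. First unblinding (A/B codes) for the statistical analyst. It comes after step 2, but its order relative to steps 3 and 4 is not stated.
6. Second unblinding, after the statistical analysis is complete.

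**Can an error found at step 3 or 4 be corrected?** The only correction route described is the query process in section 2.6.2. It stands under data entry and modification, and nothing extends it past the lock. Section 2.6.3 rules out changes after lock without exception. On the text as it stands, the answer is no.

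**Would a correction come after the codes are open?** This is possible but not required. Steps 3 and 4 could be finished between lock and first unblinding, and the text neither demands nor prevents that.

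**How sensitive is the primary outcome to a single point?**

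- Eligibility (section 2.2.2) is 17 < HAMD-17 ≤ 24, so baseline scores run from 18 to 24 and half of baseline from 9 to 12.
- Response (section 2.5.2.1) is a reduction above 50% or a score below 7. From the lowest baseline, a score of 6 is a reduction of (18 − 6)/18 = 66.7%. A score below 7 therefore always means a reduction above 50%, and status turns on the 50% line alone.
- Example with baseline 20: a week-12 score of 9 gives (20 − 9)/20 = 55%, a responder. A score of 10 gives (20 − 10)/20 = 50%, which is not above 50%.

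**Scale of one misclassification.** Section 2.3.3 plans 74 participants per group. One wrong status moves one arm's rate by 1/74 = 1.4 percentage points. The planned difference is 69 − 45.7 = 23.3 points. The number of such errors that would remain at lock is unknown.

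**The case against.** The strongest defence is that the data are not unchecked at lock. Double entry, proofreading, queries, monitoring visits and site audits of source data all come earlier, so few errors should remain, and with blinded entry nothing suggests that they would favour one arm. The sampled check also has no explicit timing, and a random sample mainly measures residual error; it cannot clean the whole dataset. The wording may simply be loose drafting in an article that condenses a fuller protocol.

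Much of this stands. The earlier controls lower the likely number of errors, and the case for the sampled check is weaker than for the line-by-line check. An unlock procedure or an error-rate threshold may well be set out in a document not shown, so its absence is no finding. What remains is that the article itself states an order in which the lock comes before verification, and no other section corrects it.

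Two stronger readings are tempting, and the document supports neither:

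- A reader might infer that corrections *would* be made with the codes open. Section 2.3.2 only permits the first unblinding once the data are locked; it does not place it before verification. The codes then opened show A/B membership, to the statistical analyst alone, and treatment identity stays sealed until the analysis is complete. The data manager, who makes corrections under section 2.6.2, is nowhere given the codes.
- A reader might infer that entry errors pass unhindered into the responder count. The controls before lock contradict that.

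**Conclusion.** The sequence in section 2.6.3 is wrong as written. Line-by-line verification is explicitly placed after a lock that allows no change, and the sampled CRF check is placed there by its position. Errors found by either check cannot be corrected under the plan's own rule. If the rule were broken, the correction could fall after the A/B codes are open to the analyst.

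The likely effect on the result is small but cannot be put in figures, because the document gives no residual error rate: each wrong responder status is worth 1.4 points in one arm, against a planned difference of 23.3. The conclusion rests on the literal wording of sections 2.6.3 and 2.3.2. If actual practice already verifies before lock, only the text needs changing.

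**What to change.** In section 2.6.3, state the order as: completion of double entry, line-by-line verification of the two entries, sampled CRF-to-EDC cross-check, resolution of the resulting queries, and then the blinded lock. In section 2.3.2, allow the first unblinding only once these steps are complete and the data are locked.

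The cost is rewording in two sections. No new check is needed, since the work already planned is done earlier. The change has to be made before lock, because afterwards the order cannot be repaired cleanly.
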